#### Background variables

The patients provide information about partnership, number and age of children living at home, education, work and sick leave by filling out a questionnaire. Information about medical situation as time points for treatment, stage of disease and comorbidity are collected from the medical record. Past illnesses and other medical problems are also reported in the questionnaire.

##### Lifestyle outcomes

The level of physical exercise is assessed by a modified Norwegian version of the Leisure Score Index (LSI) from the Godin Leisure-Time Exercise Questionnaire (GLTEQ) [50]. Dietary habits are assessed by a modified version of the SmartDiet - a short food questionnaire [51]. Smoke- and snuff habits are measured by two single questions; Do you smoke? "Yes daily", "Yes, now and then", "I smoked earlier but I have stopped" and "No, I have never smoked" and Do you take snuff? "Yes, daily", "Yes, now and then", "I snuffed earlier but I have stopped" and "No, I have never snuffed".

### Sample size and statistical considerations

LBM is the primary endpoint of the study. Sample size calculation is based on comparing the clinically relevant difference in change before and after the 16 weeks period in LBM between the EG and CG. To detect a 3 kilograms difference in change between the groups, and assuming a standard deviation (SD) of 3 kilograms, 22 patients are needed in each group with a significance level (two sided) of 5% and a power of 90%. Due to dropouts we plan to include 30 patients in each group. According to previous studies, this number should also be sufficient to detect differences in the cellular muscle outcomes (Sinha-Hikim et al., 2006).

Changes in outcome variables from start of intervention will be compared between the EG and CG groups by analysis of covariance using the baseline measurement as a covariate. P-values below 5% will be regarded as statistically significant. If obvious deviations from normal distributions are detected, changes in outcome will be compared between groups by Wilcoxon-Mann-Whitney test. The primary analysis population will be the intention to treat population using last observation carried forward to impute any missing values. In addition a per-protocol analysis including only patients with no missing observations of the variable of interest will be performed. Should imbalances in important variables be detected sensitivity analyses will also be added including these as covariates in the model.

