### Randomization

At completion of the pre-intervention assessments patients are randomized in a 1:1 ratio to the EG or CG, stratified for hospital. Randomization is computerized and performed by the staff at the clinical research office at NRH.

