#### Muscle cellular outcomes

Muscle biopsies are obtained from approximately half of the patients included in the study. Patients not willing to undergo biopsy are still eligible for trial participation.

With the patients in a supine position, a 6 mm Pelomi-needle (Albertslund, Denmark) with manual suction is used to obtain muscle samples (≈ 200 mg), under local anaesthesia (Xylocain^® ^adrenaline, 10 mg·ml^-1 ^+ 5 μg·ml^-1^, AstraZeneca, Södertälje, Sweden). Before the intervention the biopsy is obtained from the mid-section of the right vastus lateralis, and after the intervention the biopsy is obtained 3 cm proximal to the pre-intervention biopsy.

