##### Muscle fibre size and regulators of muscle fibre size

*Muscle fiber size*, measured as muscle fiber cross sectional area, represents the primary muscle cellular outcome. Secondary muscle cellular outcomes reflecting *regulators of muscle fibre size *are a) number of myonuclei per muscle fiber b) number of satellite cells per muscle fiber, c) number of satellite cells and myonuclei positive for androgen receptors and d) proteins involved in muscle protein degradation (muscle breakdown); Forkhead Box Protein O (FOXO), Ubiquitin ligase E2 and Myostatin and muscle hypertrophy; androgen receptors and growth factors such as Insulin like growth factor 1 (IGF1) and Mechano growth factor (MGF).

Muscle fibre cross sectional area and regulators of muscle fibre size are analysed by immunohistochemistry on cross sections of muscle biopsies and by western blots and enzyme-linked immunosorbent assay (ELISA) in muscle homogenate.

Muscle fibre cross sectional area will be measured by cutting transverse serial sections of the muscle biopsy (8 μm thick) with a cryostat microtome (Microm, Germany) at -22°C and mounted on glass slides. Serial sections are immunohistochemically stained for fibre types (type I and type II) (used to measure muscle fibre cross sectional area), number of satellite cells, number of myonuclei and number of satellite cells and myonuclei positive for androgen receptors. Muscle fibre cross sectional area is measured for the different fibre types separately. An image of a satellite cell and basal lamina staining on a cross section from a muscle biopsy is shown in Additional file 1.

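### The plan calls its sample size sufficient for the muscle cellular outcomes, but only about half of the patients are biopsied, so the statement covers roughly twice the number that supplies the data

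*Protocol article*

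**What the plan says.** Under Sample size and statistical considerations, the article states that "LBM is the primary endpoint of the study" and bases the calculation on it alone. The inputs are a 3 kg difference in change and an SD of 3 kg, and the result is that "22 patients are needed in each group with a significance level (two sided) of 5% and a power of 90" per cent. Enrolment is raised to 30 per group for dropouts, with no dropout rate given. The next sentence turns to the biopsy outcomes and, relying on earlier studies, says that "this number should also be sufficient to detect differences in the cellular muscle outcomes". It gives no difference, SD or power for any cellular variable.

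Under Muscle cellular outcomes, the article says: "Muscle biopsies are obtained from approximately half of the patients included in the study". Patients who decline the biopsy remain in the trial. Under Muscle fibre size and regulators of muscle fibre size, fibre cross sectional area "represents the primary muscle cellular outcome". It and all the other cellular measures come from those biopsies.

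**The concern.** The two sections do not fit together. The sufficiency statement refers to the trial's planned number, while the cellular data come from about half of it. No section gives a sample size for the biopsy subset or says that the statement was meant for that subset.

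This matters for interpretation. Cellular effects are one of the three overall aims, and the article presents them as what is new about the trial. The Discussion asks, as its main question, whether very low testosterone blunts satellite cell activation and the hypertrophic response to training. A non-significant difference between groups in fibre area could be taken as support for blunting. A reader who relied on the sample size section would believe that such a result came from a comparison of adequate size, when that comparison has about half the number stated.

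**Working it through.** **Inputs from the article**
- Lean body mass: difference 3 kg, SD 3 kg, so a standardised difference of d = 3/3 = 1.0; two-sided 5%, power 90% (Sample size and statistical considerations).
- 22 needed and 30 enrolled per group (same section).
- 1:1 allocation, stratified by hospital only (Randomization).
- About half of the patients biopsied (Muscle cellular outcomes).

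**Step 1: reproduce the plan's figure.** n per group = 2(z₀.₉₇₅ + z₀.₉₀)²/d² = 2(1.960 + 1.282)²/1² = 21.01, which rounds up to 22. The two-sample t-test solution is 22.02, and power at exactly 22 is 90.0%. The calculation for lean body mass is correct.

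**Step 2: implied dropout.** 1 − 22/30 = 8/30 = 26.7%. The article does not state this rate; it is back-calculated.

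**Step 3: size of the biopsy subset.** At enrolment: 0.5 × 30 = 15 per group. With a real post-intervention biopsy, for a range of assumed dropout rates:
- 0%: 15
- 10%: 15 × 0.90 = 13.5
- 20%: 15 × 0.80 = 12
- 26.7%: 15 × 22/30 = 11

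The sentence can be read as referring to the 30 enrolled or to the 22 needed. Half of the first is 15 and half of the second is 11, so the mismatch is a factor of about two on either reading.

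**Step 4: what that size can detect.** The article gives no cellular effect size or SD, so d is varied as an assumption. Power is for a two-sided 5% unadjusted t-test with noncentrality d√(n/2) and 2n − 2 degrees of freedom.

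| Assumed d (SD units) | n = 30 | n = 22 | n = 15 | n = 11 |
|---|---|---|---|---|
| 0.8 | 86% | 74% | 56% | 43% |
| 1.0 | 97% | 90% | 75% | 61% |
| 1.2 | 99.5% | 97% | 89% | 76% |
| 1.5 | >99% | >99% | 98% | 92% |
| d detectable with 90% power | 0.85 | 1.00 | 1.23 | 1.45 |
| d detectable with 80% power | 0.74 | 0.87 | 1.06 | 1.26 |

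**Step 5: uneven split.** Because randomisation is not stratified by biopsy consent, 15 and 15 is only the expected split of 30 biopsied patients. A 10/20 split would give 70% power at d = 1.0, against 75% for an even split.

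**The case against.** The strongest reply is that the article contains no evidence of inadequate power. A reader might infer from the table that the cellular comparison has 61% power, or that it is simply too small. The documents do not support that, for these reasons:

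- **Effect size.** d = 1.0 is the lean body mass assumption. The Background cites increases in fibre area of 10–60% with training but gives no SD, so the relevant d could lie well above or below 1. At 1.5 SD, even 11 per group would have 92% power. The earlier work behind the sufficiency sentence cannot be assessed from the article.
- **Number of pairs.** Eleven per group is not a stated figure. Thirty may simply be a round number, patients who accept biopsy may drop out at a different rate, and the stated half might already mean patients with samples, in which case applying dropout again would count it twice. Under the planned intention-to-treat analysis with last observation carried forward, about 15 per group would nominally be analysed, although a carried-forward baseline biopsy tells us nothing about change.
- **Method.** The plan specifies analysis of covariance with baseline as covariate, which could do somewhat better than the t-test used here.
- **Importance.** Fibre area is primary only among the cellular outcomes. Lean body mass is the trial's primary endpoint, and its sample size is sound.

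All of these stand, and they limit the point to an inconsistency illustrated with a range. They do not remove it. The sentence attaches sufficiency to the planned trial number, and the design delivers about half of that number for these outcomes at any dropout rate. Nor is this a complaint that a cellular power calculation was left to another document: the article makes an adequacy statement, and another of its sections contradicts the number it rests on.

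**Conclusion.** The point holds as an internal inconsistency. Sufficiency for the cellular outcomes is asserted for 30 (or 22) per group, while the biopsy plan supplies about 15 per group at enrolment and about 11 to 15 with paired samples. Relative to the stated size, the difference detectable with 90% power rises from 0.85 SD (30) or 1.00 SD (22) to between 1.23 SD (15) and 1.45 SD (11).

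These figures assume an even split of biopsied patients, an unadjusted t-test and, for the lower number, the implied 26.7% dropout. They show how far the claim shifts; they do not prove that the subset is too small.

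The sentence should be corrected, because it bears on a stated aim and on how a null cellular result is read. The primary analysis, the enrolment target and the randomisation are not affected.

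**What to change.** Replace the sufficiency sentence in Sample size and statistical considerations with one that refers to the expected biopsy subset, by either of two routes:

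1. State that about 15 patients per group are expected to be biopsied and about 11 to 15 to have paired samples. Give the difference in fibre cross sectional area detectable at that size, using the sponsor's own assumed difference and SD and its own dropout assumption.
2. Where no such assumption can be supported, label the cellular outcomes exploratory and report them as estimated differences with 95% confidence intervals.

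Either route prevents a non-significant cellular result from being taken as adequately powered evidence of blunted adaptation. No additional patients, biopsies or procedures are required. The cost is a change of wording and a less favourable statement about the cellular outcomes.

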### Participants

Patients are included from two oncological units at Oslo University hospital, the Norwegian Radium Hospital (NRH) and Ullevaal University Hospital (UUH). All patients must fulfill the following eligibility criteria 1) PC cancer of intermediate or high-risk profiles, 2) high-dose radiotherapy with or without two high-dose-rate brachytherapy fractions [43], 3) (neo)-adjuvant ADT by commercially available LHRH analogue for 9-36 months. The most important inclusion and exclusion criteria are 1) less than one hour car drive between the patient's residence and the place of training or 2) current regular strength training. All inclusion and exclusion criteria are listed in Additional file 2.

In addition to written information, eligible patients are verbally informed about the study by their responsible radiotherapist and the study coordinator usually during or immediately after radiotherapy. After giving their written consent agreeing patients are scheduled for pre-intervention assessments usually 1-2 months after radiotherapy, which are repeated one week after the intervention period (Figure 3).

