**Figure 3 F3:**
[figure not shown]
**Timeline in the PEPC trial**. Different duration of ADT related to different risk groups and somehow different treatment strategies in the two hospitals. Importantly all patients are on ADT at pre- and post-intervention assessments.

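### Randomisation is stratified by hospital, but the stated ANCOVA omits hospital; if hospital predicts LBM change, the standard error is too large and the test conservative

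*Protocol article*

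**What the plan says.** Under Participants: "Patients are included from two oncological units at Oslo University hospital". Under Randomization: "patients are randomized in a 1:1 ratio to the EG or CG, stratified for hospital". The method used to keep the arms balanced within each hospital is not described.

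Under Sample size and statistical considerations: "LBM is the primary endpoint of the study". Changes in outcome variables "will be compared between the EG and CG groups by analysis of covariance using the baseline measurement as a covariate". No other term is named for that model. On further covariates the section adds: "Should imbalances in important variables be detected sensitivity analyses will also be added including these as covariates in the model". It lists no variables and gives no criterion for imbalance.

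The Figure 3 legend is the one place that suggests the hospitals may differ in a way that matters: "Different duration of ADT related to different risk groups and somehow different treatment strategies in the two hospitals". It also notes that every patient is on ADT at both assessments.

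**The concern.** A factor used to stratify randomisation normally belongs in the analysis model. Stratification with balanced allocation makes the arms alike on hospital, so differences between hospitals add little or nothing to the error of the arm comparison. If the model has no hospital term, that variation stays in the residual variance and enters the standard error anyway. The confidence interval is then wider than it should be, and the true type I error falls below 5%.

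What is at stake is some of the precision that stratification was meant to secure. There is no added risk of a false positive. The article names the method and its covariate, so this is a mismatch between the stated design and the stated model, not merely a detail left to an unseen analysis plan.

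**Working it through.** **Inputs from the article.** Two hospitals, 1:1 allocation stratified by hospital. "To detect a 3 kilograms difference in change between the groups", and "assuming a standard deviation (SD) of 3 kilograms". Two-sided 5% level, 90% power, 22 per group, and 30 per group planned to allow for dropout.

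**Assumed, because the article gives no figure.** R², the share of variance in LBM change explained by hospital beyond baseline LBM, ranges from 0 to 20%. The hospitals are of equal size, the arms are exactly balanced within each, and the SD of 3 kg includes the between-hospital part.

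**Step 1: reproduce the plan's figure.** n per group = 2 × (1.960 + 1.282)² × (3/3)² = 21.01, rounded up to 22. The noncentral t gives 89.97% power at 22 per group. The stated figure stands.

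**Step 2: inflation of the standard error.** With hospital in the model the residual SD is 3 × √(1 − R²). Omitting it inflates the standard error by 1/√(1 − R²):

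- R² 5%: 1/√0.95 = 1.026
- R² 10%: 1/√0.90 = 1.054
- R² 20%: 1/√0.80 = 1.118

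**Step 3: what each R² implies.** With equal hospitals, the difference in mean LBM change between them is √(R² × 9 / 0.25) = 6 × √R² kg. That is 0.6 kg at 1%, 0.85 kg at 2%, 1.34 kg at 5%, 1.90 kg at 10% and 2.68 kg at 20%.

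**Step 4: patients needed with hospital in the model.** n = 21.01 × (1 − R²), rounded up: 22 at 0%, 21 at 1% or 2%, 20 at 5%, 19 at 10%, 17 at 20%.

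**Step 5: simulation.** 15,000 runs per cell, ANCOVA on baseline without and with hospital. Monte Carlo error is about 0.2 points for type I error (√(0.05 × 0.95/15,000) = 0.0018).

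| Per group | R² | Type I error without / with hospital | Power without / with hospital |
|---|---|---|---|
| 22 | 0% | 4.8% / 4.8% | 89.1% / 89.1% |
| 22 | 5% | 4.0% / 4.4% | 89.4% / 90.4% |
| 22 | 10% | 3.8% / 4.8% | 90.1% / 92.0% |
| 22 | 20% | 3.1% / 5.2% | 91.4% / 95.0% |
| 30 | 0% | 4.6% / 4.6% | 96.5% / 96.4% |
| 30 | 5% | 4.7% / 5.2% | 96.8% / 97.1% |
| 30 | 10% | 4.0% / 5.2% | 97.0% / 97.7% |
| 30 | 20% | 3.2% / 5.2% | 97.7% / 98.8% |

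The simulated standard errors agree with step 2. At 22 per group and R² 20%, for example, they average 0.9149 without hospital and 0.8146 with it, a ratio of 1.12. At R² 0% they are 0.9090 and 0.9092, so the extra degree of freedom costs next to nothing. The power difference is a gain forgone. Power without hospital does not drop as R² rises.

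**The case against.** **The evidence that hospital is prognostic is thin.** The Figure 3 legend attributes the differing ADT durations to risk group as well as to hospital strategy. The eligible range of 9 to 36 months is total duration, much of which can fall after the 16-week window. Both units belong to one university hospital, and all training takes place at one site. The larger R² values also look generous. The Background cites a 3% LBM loss over 6 to 12 months of ADT. If LBM is 50 to 65 kg (an assumption), that is 1.5 to 1.95 kg for the whole ADT effect, while R² of 10% or 20% needs a gap between hospitals of 1.9 or 2.7 kg within 16 weeks. An R² of 1 to 2% is easier to credit and changes the required number by one per group. This stands: the loss is conditional and probably small.

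**The error is in the safe direction.** This also stands. No positive result would be put in doubt.

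A reader might also draw three stronger conclusions, which the article does not support:

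- *That the primary adjustment is data-driven.* It is not. The primary model is fixed in advance, and a detected imbalance only adds sensitivity analyses.
- *That the imbalance rule can never bring hospital in.* Stratification makes that unlikely, but no balancing method within hospital is stated, so a chance imbalance cannot be excluded. In that case the conservatism shrinks too.
- *That the sample size is wrong.* The 22 per group reproduces, and omitting hospital does not make it too small.

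**Conclusion.** The point holds as a minor mismatch that is nearly free to correct: hospital defines the randomisation strata and is absent from the stated ANCOVA. The cost of the omission depends on whether hospital predicts LBM change beyond baseline LBM, which the article makes plausible but does not quantify. If it does not, nothing is lost. For an assumed R² of 5 to 20%, the standard error is about 2.6% to 11.8% too large and type I error at 22 per group falls to about 4.0% to 3.1%. At R² 20% the power forgone is 95.0 − 91.4 = 3.6 points at 22 per group and 98.8 − 97.7 = about 1 point at 30. These figures assume equal hospitals and exact balance within each.

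**What to change.** State the primary model as change in LBM (or post-intervention LBM) = arm + baseline value + hospital, with hospital as a fixed factor. Use the same model for the other outcomes analysed by ANCOVA.

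The cost is one line of text and one residual degree of freedom (41 to 40 with 44 patients, 57 to 56 with 60). Hospital is known from randomisation, so no new data are needed, and the sample size stays as it is.

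Optionally, name the covariates for the sensitivity analyses in advance instead of waiting for an imbalance. That is a matter of preference, and the point does not depend on it.

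### The fallback from ANCOVA to an unadjusted Wilcoxon test discards baseline and the difference in kg, and the plan's own LOCF zeros can set it off

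*Protocol article*

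**What the plan says.** All of this is in the Protocol article, Sample size and statistical considerations, unless noted.

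- Primary endpoint: "LBM is the primary endpoint of the study". It is sized on the kg scale: "To detect a 3 kilograms difference in change between the groups", "assuming a standard deviation (SD) of 3 kilograms", so that "22 patients are needed in each group with a significance level (two sided) of 5% and a power of 90" percent. Recruitment is then raised: "Due to dropouts we plan to include 30 patients in each group".
- Default analysis: changes are compared between arms by ANCOVA with the baseline value as covariate.
- Fallback: "If obvious deviations from normal distributions are detected, changes in outcome will be compared between groups by Wilcoxon-Mann-Whitney test". No outcome is exempt, so the rule covers LBM. No covariate is named. The text does not say how large a deviation counts, or whether raw changes or model residuals are inspected.
- Missing data: the primary analysis is by intention to treat, "using last observation carried forward to impute any missing values". A second analysis uses only patients with no missing values.
- Outcomes and assessments describes one assessment before and one after the intervention.

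**The concern.** The fallback differs from the default in more than the distributional assumption. It discards a baseline value that has already been collected, and it replaces an adjusted mean difference in kg by a rank comparison of raw changes. The quantity reported for LBM would then depend on how the data happen to look.

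The rule also interacts with LOCF. With only two assessments, the last observation before a missing post value is the baseline, so the imputed change is exactly zero. A stack of zeros in each arm can make normally distributed changes look non-normal. The switch could then be made because of the imputation and not because of the outcome. At stake are some power, an interpretable primary estimate, and a better analysis of the skewed secondary outcomes.

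**Working it through.** **1. The plan's own figure.** Difference 3 kg, SD of change 3 kg, two-sided 5%, power 90%. An exact two-sample t calculation gives n = 22.02 per group, and 89.97% power at 22. The stated 22 is reproduced. It is an unadjusted comparison of changes and counts no gain from the baseline covariate. Going from 22 to 30 leaves 8 of 30 = 26.7% for dropout.

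**2. What dropping baseline costs in variance.** With equal pre and post SDs and baseline-post correlation r, the variance ratio of change score to ANCOVA is 2(1 - r)/(1 - r²) = 2/(1 + r). This is 1.54, 1.33, 1.18 and 1.05 at r = 0.3, 0.5, 0.7 and 0.9. The document does not give r. For total LBM a value near 0.9 is plausible (assumption), so the loss there is about 5%. On normal data the Wilcoxon test also has asymptotic efficiency 3/π = 0.955 relative to the t-test.

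**3. The switching rule with complete normal data.** Simulation at 22 per group, true effect 3 kg, SD of change 3 kg. The baseline-change correlation ρ is assumed; with equal SDs, r = 1 - 2ρ². A Shapiro-Wilk test at 5% on each arm's changes stands in for the undefined criterion.

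| ρ (implied r) | fixed ANCOVA | switching rule | always Wilcoxon |
|---|---|---|---|
| 0 (1.00) | 88.9% | 88.8% | 87.8% |
| -0.3 (0.82) | 92.2% | 92.0% | 89.0% |
| -0.5 (0.50) | 96.0% | 95.4% | 88.8% |
| -0.7 (0.02) | 99.1% | 98.1% | 87.3% |

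The rule costs at most about 1 point here, because it rarely fires (about 10% of trials).

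**4. The same rule with LOCF zeros.** 30 per group, normal underlying data, 8 post values per arm replaced by baseline, same effect and SD.

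| ρ (implied r) | per-arm check fires | residual check fires | fixed ANCOVA | switching rule (per-arm check) | loss |
|---|---|---|---|---|---|
| 0 (1.00) | 77.6% | 28.0% | 87.6% | 84.5% | 3.1 points |
| -0.3 (0.82) | 77.4% | 20.1% | 90.4% | 86.3% | 4.1 points |
| -0.5 (0.50) | 77.3% | 12.0% | 93.4% | 85.8% | 7.6 points |

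With no zeros the per-arm check fires in about 10% of trials and the residual check in about 5%.

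- Across further simulations at 8 of 30, the per-arm check fired in about 73-78% and the residual check in about 14-23%. The loss was about 5-9 points at moderate correlations.
- At r = 0.9, ρ = -√((1 - 0.9)/2) = -0.22. That lies between the first two rows, so the loss is about 3-4 points.
- With fewer zeros the per-arm check fires less often: 16-17% at 3 of 30 and 33% at 5 of 30.
- With no treatment effect and 8 of 30 zeros it fires in 58-61%.

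**5. Truly skewed outcomes.** 22 per group, lognormal baseline and post values, effect 0.8 SD on the log scale.

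| r | ANCOVA, untransformed | Wilcoxon on change | rank ANCOVA keeping baseline |
|---|---|---|---|
| 0.3 | 57% | 59% | 74% |
| 0.5 | 62% | 72% | 80% |
| 0.7 | 75% | 89% | 92% |

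ANCOVA on the logged values is ordinary normal ANCOVA at 0.8 SD: 76%, 84% and 95%. Rank ANCOVA here regresses the rank of the post value on group and the rank of baseline; ranking the change recovers less.

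**6. Type I error.** Under the switching rule it was 3.9-5.4% in all null settings: normal, lognormal and heavy-tailed errors, with and without LOCF zeros.

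**The case against.** A rank fallback for non-normal data is conventional and is prespecified here. How normality is judged and which variables are logged are often left to an SAP, and none is shown. This stands as far as the undefined criterion goes. It does not cover the fallback itself, which the article states and which names no covariate.

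The trigger rests on assumptions. Thirty per arm is a recruitment allowance, not a forecast that 8 will be missing. The wording may mean a look at a plot, where a stack of imputed zeros would be recognised. A check on residuals fires far less often than a per-arm test. The analysis restricted to patients with complete values contains no such zeros. All of this limits the size of the problem, but the LOCF analysis is the primary one and nothing in the text says that imputed values are set aside before normality is judged.

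Two stronger readings are tempting. A reader might infer that choosing the test from the data inflates the 5% error rate; the simulations show no inflation. A reader might also infer that the switch costs substantial power for skewed outcomes such as CRP or muscle proteins, from a comparison on normal data (76% against 56% at r = 0.3, 22 per group, effect 0.8 SD). With complete normal data, however, the rule mostly stays with ANCOVA. On truly skewed data Wilcoxon on change matches or beats untransformed ANCOVA. With lognormal errors on the change itself, for example, ANCOVA had 90-93% and Wilcoxon 98-99.9%.

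**Conclusion.** The point holds in a limited form. The text shows that the fallback drops baseline adjustment and the kg estimate for every outcome, LBM included, and that LOCF with two assessments yields changes of exactly zero.

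- **LBM: minor.** The cost is about 1 point of power with complete normal data. It is about 3-4 points if 8 of 30 per arm are missing, the check is a per-arm Shapiro-Wilk test and r is near 0.9. The larger loss is the estimate in kg.
- **Secondary outcomes: moderate.** At moderate correlation the LOCF-triggered switch costs about 5-9 points under the same assumptions about dropout and check. For skewed outcomes the stated fallback is defensible against untransformed ANCOVA, but it gives up 15, 8 and 3 points (74 - 59, 80 - 72, 92 - 89) against a rank analysis that keeps baseline.

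The correlations, the missing rate and the form of the normality check are assumptions; the document gives none of them.

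**What to change.** 1. Make baseline-adjusted ANCOVA the fixed analysis of LBM, whatever a normality check shows, and report the adjusted difference in kg with its confidence interval.
2. For skewed outcomes, replace the unadjusted Wilcoxon fallback with one that keeps baseline: ANCOVA on the log scale for outcomes named in advance (for example CRP and protein levels), or rank ANCOVA of the post value on baseline.
3. Where normality is still examined, use model residuals from observed values, not LOCF-imputed ones.
4. Keep the plain Wilcoxon test on changes as a sensitivity analysis.

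The cost is a change of wording and minor programming, with no effect on design or recruitment. The one real downside is that a rank analysis gives no estimate in original units, which is a reason to prefer a named log transformation where it fits.
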